**Further analysis**		
**Outcome variables**	**Predictor variables**	**Possible confounders**
Access to chemotherapy	Age on diagnosis Family income Distance to hospital Who pays for ovarian cancer care Resource level of participating site	Stage of ovarian cancer Date of diagnosis Use of neoadjuvant chemotherapy
Access to optimal cytoreductive ovarian cancer	Age on diagnosis Family income Distance to hospital Who pays for ovarian cancer care Resource level of participating site	Date of diagnosis Use of neoadjuvant chemotherapy
Levels of awareness of ovarian cancer	Education level Family income level Distance to hospital Family history	
Time to seek help for symptoms	Age Education level Family income level Who pays for ovarian cancer care First person consulted re symptoms Number of visits prior to diagnosis Level of concern over symptoms Type of symptoms Number of symptoms	

We will perform descriptive and inferential statistics, overall and by country and economic grouping using statistical softwares such as STATA and R. Categorical variables will be summarised with counts and percentages, with Chi Squared Tests or Fisher’s Exact Test used to compare proportions between groups. Continuous variables, such as time to diagnosis, will be examined graphically and summarised using appropriate metrics (mean and standard deviation or median and interquartile range depending on the distribution of the variable data). Tests, such as Kruskal-Wallis, will be applied to continuous variables. Outlying countries will be identified and described.

Appropriate regression analysis approaches will be used to examine assocations between independent and outcome variables. Binary, ordinal or nominal regression will be used depending on the nature of the outcome variable. Univariable regression will be employed to examine individual associations and multivariable regression to examine combined assocations between predictor and outcome variables.

The two free-text answers will be translated, coded and analysed using qualitative content analysis to identify categories and possible themes.

Each country will receive a bespoke report summarising their results, how these compare with the average for all participants at a global and/or regional level, and provide information about the context of ovarian cancer care in their country obtained through interviews and surveys with the CLCs. CLCs will ‘own’ the country specific data and will be encouraged to share their national findings, and utilise them for healthcare planning, further research and engagement activities in their country.

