### Data collection procedure

The administrator generates a unique identifier number (UIN) for the ovarian cancer patients on REDCap and some basic demographic and clinical data is entered to determine eligibility (S6 File). This information includes age at diagnosis, month and year of diagnosis, type and stage of ovarian cancer and current treatment status. This provides an overview of women attending the clinics and allows basic comparisons between the groups who do and don’t consent.

Women with ovarian cancer are then approached and taken through an informed consent process. They are given written and verbal information about the study. If they are not attending clinics directly, they can be sent this information by email or be spoken to by phone. They are taken through the purpose and outline of the study and the risks and benefits of taking part are discussed. They are informed that they do not have to participate, they do not have to answer every question, and that they can withdraw their information up to 3 months after the close of data collection. They are then asked whether or not they consent to participate in the study and if they consent, whether they wish to i) self-complete a paper survey, ii) self-complete the survey via a secure email link, iii) self-complete the survey via a secure WhatsApp link (or other online messaging app), or iv) whether they wish to have the administrator ask them the questions. Their decision is recorded. Women who receive the information in person, or by phone need to record their consent in writing, and a copy is kept in a secure location on site. In addition to the standard consent form for the study, some local sites require patients to also complete their own informed consent forms, as part of the ethics approval. One country asked for women to consent with a thumbprint. Women who receive the information by email or WhatsApp can consent electronically at the start of the survey, or they can request an administrator contact them if they have questions before deciding.

Local teams are encouraged to supply the women with some written as well as verbal information about ovarian cancer, including at least two sources of potential support and information, be they non-governmental organisations (NGO), charities, or other groups (S6 File). The process is summarised in Fig 3.

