### Data analysis

In our analysis, we seek to examine variation in key metrics (such as stage of ovarian cancer, time to diagnosis and levels of awareness) by country, region and by the socio-economic country group. In addition, we will explore associations between patient and country characteristics and key outcome measures. Table 3 gives some examples of the outcome variables and expected areas for further analysis.

**Table 3 pone.0298154.t003:** Outcome variables and expected further analysis.

Outcome variables		
• Access to chemotherapy • Access to optimal cytoreductive surgery • Access to genetic testing • Level of ovarian cancer knowledge • Time to seek help • Time from seeking help to obtaining a diagnosis • Time from diagnosis to treatment • Information needs •Impact on family finances •Priorities for action		

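### Table 3 lists neoadjuvant chemotherapy as a possible confounder of access to chemotherapy, although as the outcome stands it is part of it

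*Protocol article*

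**What the plan says.** The Data analysis section introduces the table in open terms: "Table 3 gives some examples of the outcome variables and expected areas for further analysis". Its lower part pairs outcomes with predictors and with a column headed "Possible confounders". Two rows concern access to treatment, and both have the same predictors: "Age on diagnosis Family income Distance to hospital Who pays for ovarian cancer care Resource level of participating site".

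- **Access to chemotherapy.** Possible confounders: "Stage of ovarian cancer Date of diagnosis Use of neoadjuvant chemotherapy".
- **Access to optimal cytoreductive surgery**, printed in this part of the table as "Access to optimal cytoreductive ovarian cancer" but named as surgery in the outcome list above it. Possible confounders: "Date of diagnosis Use of neoadjuvant chemotherapy". Stage is not listed.

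On the model, the text says: "Binary, ordinal or nominal regression will be used depending on the nature of the outcome variable". Univariable and multivariable models are both planned. The Data collection procedure section says that the information entered for each woman to determine eligibility includes "month and year of diagnosis, type and stage of ovarian cancer and current treatment status".

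**The concern.** A confounder is a separate variable that influences the outcome. Neoadjuvant chemotherapy is itself chemotherapy, so a woman recorded as having had it cannot be recorded as lacking access, unless the outcome is defined to exclude it. Adjusting for it conditions on part of the outcome.

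The access models are meant to show whether income, distance, payer or site resource go with access to treatment, and the country reports are intended to feed healthcare planning. With this covariate in the model, those odds ratios answer a narrower question than the row label suggests, and the table does not say so.

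The difference between the two rows on stage is a smaller matter. With identical predictors, a reader cannot tell what role stage is meant to play.

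**Working it through.** The plan states no figure on this point, so there is none to reproduce. The first step is algebra; the sizes in steps 2 and 3 rest on assumptions, because the article gives no neoadjuvant rates and no relation of stage to income.

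**1. Separation.** Let Y = 1 for any chemotherapy, Z = 1 for neoadjuvant use, x the predictors, and logit P(Y = 1) = a + bx + cZ. Every woman with Z = 1 has Y = 1, so her likelihood contribution is 1/(1 + exp(−(a + bx + c))). This tends to 1 as c grows, whatever b is. The likelihood is maximised as c goes to infinity, and only women with Z = 0 then inform b. If access were coded in more than two levels, neoadjuvant use would still rule out the no-access level.

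**2. Effect on a predictor's odds ratio.** For a given income group and stage, let p be the probability of any chemotherapy and s the share of treated women who had it as neoadjuvant treatment. Among women with Z = 0 the odds of chemotherapy are p(1 − s)/(1 − p). Therefore

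adjusted OR = OR × (1 − s₁)/(1 − s₀),

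with 1 for higher and 0 for lower income. If s₁ = s₀ the factor is 1.

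Assumptions: half the women have higher income; the log-odds ratio of chemotherapy on income is 0.8, so the OR is exp(0.8) = 2.23; s is centred on 20%, 40% or 60%; the log-odds ratio of neoadjuvant timing on income among treated women is 0, +0.7 or −0.7. The simulation used 400,000 women with stage in the model, and was run with stage related and unrelated to income. It gave 2.21 to 2.25 without the neoadjuvant covariate.

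| Centre of s | Timing and income | s₁, s₀ | Factor | OR by formula | OR simulated |
|---|---|---|---|---|---|
| any | unrelated | equal | 1 | 2.23 | 2.20–2.26 |
| 20% | higher income, more neoadjuvant | 26.2%, 15.0% | 0.868 | 1.93 | 1.94 |
| 20% | higher income, less | 15.0%, 26.2% | 1.152 | 2.56 | 2.57–2.58 |
| 40% | more | 48.6%, 32.0% | 0.755 | 1.68 | 1.68–1.69 |
| 40% | less | 32.0%, 48.6% | 1.324 | 2.95 | 2.92–2.98 |
| 60% | more | 68.0%, 51.4% | 0.657 | 1.46 | 1.45–1.46 |
| 60% | less | 51.4%, 68.0% | 1.521 | 3.38 | 3.37–3.41 |

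Formula and simulation agree. The share of women with chemotherapy given neoadjuvant use was 1.00 in every run.

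**3. Stage in the surgery row.** Assumptions: the log-odds ratio of optimal surgery is 0.5 on income (OR exp(0.5) = 1.65), −1.2 on advanced stage and 0.2 on neoadjuvant use. The log-odds ratio of advanced stage on income varies. Neoadjuvant use stays in the model, as in Table 3.

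| Log-OR of advanced stage on income | Income OR with stage | Income OR without stage |
|---|---|---|
| 0 | 1.65 | 1.61 |
| −0.35 | 1.65 | 1.76 |
| −0.7 | 1.65 | 1.93 |
| −1.1 | 1.64 | 2.15 |

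In this simulation stage is generated from income, so it lies on the path from income to surgery. The right-hand column then includes the part of the association that runs through stage. The gap shows that the two models answer different questions, not that one of them is biased.

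**The case against.** Four things can be said for the plan.

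- **No model is fixed.** The column lists possible confounders and the table gives examples. The stated hypothesis concerns variation between countries, and associations are explored in addition. This stands and lowers the weight of the point. It does not make a component of the outcome a sound candidate for adjustment.
- **The outcome is not defined here.** If access means chemotherapy other than neoadjuvant, the objection falls away. This stands as a condition. The article says nothing of the kind, and the plain reading includes neoadjuvant treatment.
- **Univariable models are also planned**, so an unadjusted odds ratio would appear beside the adjusted one, and an analyst would probably notice the perfect prediction. This limits the harm. But dropping the covariate together with the women it predicts leaves exactly the restricted model of step 1, so noticing it does not settle what to report.
- **Stage may be a mediator.** Late stage may be one way in which low income or long distance reduces access to surgery. This stands, and it is why the absence of stage from the surgery row is an unexplained difference rather than an error.

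A reader might infer that both access models are bound to give biased associations. The documents do not support that. In the chemotherapy model the distortion depends on neoadjuvant timing being related to the predictors. In the surgery model the answer depends on whether total or direct associations are wanted, which the article does not say.

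**Conclusion.** The chemotherapy row is wrong as written, provided that access means any chemotherapy. On that reading the separation and the restriction to women without neoadjuvant use follow with certainty. The shift in the predictor odds ratios is conditional: from about 2.2 to between 1.5 and 3.4 under the assumed parameters, and none when the neoadjuvant share among treated women is the same across predictor levels. These are illustrations, not estimates for the study. In the range tried the odds ratio stayed above 1, so no reversal was shown, although the formula does not rule one out under stronger differences.

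The stage point is a secondary clarification. A reader might also want tumour type in both rows, but its absence from a list of examples contradicts nothing and is not part of this point.

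**What to change.** 1. In the chemotherapy row of Table 3, delete neoadjuvant use from the possible confounders. Alternatively, define the outcome explicitly as chemotherapy other than neoadjuvant; this asks a narrower question and needs a stated rule for coding women who had neoadjuvant treatment only. In either case report neoadjuvant use descriptively or as a separate outcome.
2. Report the surgery model with and without stage, and say in a sentence that stage may be a confounder or a mediator. Correct the row label so that it names surgery.

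The cost is an edit to two rows of the table, one sentence and one further model. No new data are needed, since stage is already entered for every woman. The change is best made before the regression analyses are run.

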Route to diagnosis 14 questions	Q.21	For women who said they experienced symptoms Which type of person, other than a family member, did you **first** seek advice from, about your symptoms? **SELECT ONLY** **ONE** **ANSWER** • A local healer • An alternative health practitioner • A family doctor • A gynaecologist • A gynaecologic oncologist (a doctor specialising in the treatment of ovarian cancer) • A gastroenterologist • An emergency room or accident and emergency doctor • A nurse • A pharmacist • Someone else
Treatments for ovarian cancer 9 questions	Q.29	In deciding what, if any, treatments you will have to control your ovarian cancer or deal with side effects from treatment, which of the following will affect your decision? **TICK ALL THAT APPLY** • The opinion of the doctor • The opinion of my family • I will make up my own mind • The cost of treatment drugs • Other costs associated with treatment such as transport or accommodation • The chance to cure or extend my life • The side effects of treatment • None of the above
Emotional support needs 7 questions	Q.38	For women who have experienced support needs Are there particular issues you have faced? **TICK ALL THAT APPLY** • Fear of the cancer returning • Fear that treatment will not work • Fear of dying • Difficulty with getting back to ‘normal life’ after treatment • Partner or spouse leaving • Other issues relating to family and friends • Feelings of isolation • Feeling unable to talk to others • Loss of fertility • Regaining sexual intimacy with a partner • Coping with the menopause • Dealing with stigma because of the cancer diagnosis • Other • None in particular
Practical support needs 5 questions	Q.47	Has having a diagnosis of ovarian cancer had an impact on your financial situation? **SELECT ONLY** **ONE** **ANSWER** • Yes to a great extent • Yes to some extent • Not much • Not at all • I would prefer not to say

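### Table 3 lists the number of visits before diagnosis as a predictor of time to seek help, although those visits accumulate after that interval has ended

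*Protocol article*

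**What the plan says.** The upper part of Table 3 (Data analysis) names two adjacent intervals as distinct outcomes: "Time to seek help • Time from seeking help to obtaining a diagnosis". The lower part (Further analysis) has a row whose outcome is "Time to seek help for symptoms". Its predictor cell names age, education, family income, who pays for care, and symptom type and number, and also "First person consulted re symptoms Number of visits prior to diagnosis Level of concern over symptoms". The confounder cell of that row is empty.

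The text after the table plans univariable regression and then "multivariable regression to examine combined assocations between predictor and outcome variables". Nothing there treats the visit count or the first person consulted differently from the other predictors.

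Table 1 shows how the first person consulted is measured. Question 21, put to women who reported symptoms, asks which type of person outside the family they first went to "seek advice from, about your symptoms". The answers include a local healer, an alternative practitioner and a pharmacist as well as doctors and nurses.

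The article describes the status of the table as follows: "Table 3 gives some examples of the outcome variables and expected areas for further analysis". The stated purpose is that "we will explore associations between patient and country characteristics and key outcome measures".

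**The concern.** A predictor of an interval should be in place before the interval ends. The visit count is not: it starts when help is sought and runs on to diagnosis. It may also depend on the delay itself. A woman who presents late with obvious disease may need fewer visits, for example.

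If education or income also influences the number of visits, the count is a common effect of the delay and of the predictors of interest. Adjusting for it then creates or distorts an association between them. The coefficients at risk are those for education, income and payer, which a reader would use to judge who delays seeking help and why. The visit count would also show a coefficient of its own that looks like a cause of delay but partly reflects a consequence of it.

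**Working it through.** The plan gives no figure on this point, so there is none to reproduce. The check is one of time order, followed by two illustrations on assumed values.

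**Time order.** Because Table 3 separates the time to seek help from the time between seeking help and diagnosis, the first interval closes when help is sought. The sequence is:

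1. Symptoms start.
2. Time to seek help runs.
3. Help is sought, and the first person consulted becomes known (question 21).
4. Visits accumulate.
5. Diagnosis.

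The visit count belongs to step 4, after the outcome is complete. The first person consulted is observed at step 3, when the interval ends.

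**Illustration 1: no true association.** Let education and delay be uncorrelated, and let r1 and r2 be their correlations with the visit count. Both are assumed to have the same sign, because the article gives no such correlations. The partial correlation of education and delay given visits is -(r1 × r2) / √[(1 - r1²)(1 - r2²)]. The z value is atanh(partial r) × √(n - 4), shown in absolute value. It uses n = 2,160, the sum of the country minima in Table 2, so √2156 = 46.4.

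| Assumed \|r1\| = \|r2\| | Partial correlation | z at n = 2,160 |
|---|---|---|
| 0.1 | -0.01/0.99 = -0.010 | about 0.5 |
| 0.2 | -0.04/0.96 = -0.042 | about 1.9 |
| 0.3 | -0.09/0.91 = -0.099 | about 4.6 |

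These z values are upper illustrations. They treat women as independent although they are clustered in 113 sites and 24 countries. They also use the full planned number although question 21 goes only to symptomatic women. If the effective sample size were half (an assumption), 4.6 would fall to about 4.6/√2 = 3.3. The partial correlation itself does not depend on n.

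**Illustration 2: a true effect.** Let delay T = -0.3 × education + noise, and visits V = g × T - 0.3 × education + noise, with unit-variance noise and all coefficients assumed. Regressing T on education alone recovers -0.30. With V added, the education coefficient is (-0.3 + 0.3g)/(1 + g²) and the coefficient of V is g/(1 + g²).

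| g (effect of delay on visits) | Education coefficient | Coefficient of visits |
|---|---|---|
| 0 | -0.30 | 0 |
| 0.3 | -0.21/1.09 = -0.19 | 0.28 |
| 0.6 | -0.12/1.36 = -0.09 | 0.44 |

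A simulation of 200,000 records gave -0.30, -0.19 and -0.09 for education, and 0.00, 0.27 and 0.44 for visits, which agrees. If late presenters have fewer visits, g is negative: at g = -0.3 the education coefficient is -0.39/1.09 = -0.36, an exaggeration. So the bias can go either way, and it vanishes if delay does not affect visits.

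**The case against.** Table 3 offers examples, the aim is to explore associations, and the article does not say that every listed predictor enters one model. Univariable results for education and income are untouched. This limits the weight of the point but does not remove it. The visit count is printed as a predictor of this outcome, joint modelling of predictors is planned, and an education coefficient conditional on later visits is hard to interpret even as an association.

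Three stronger readings are tempting, and the article does not support them.

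- **The first person consulted cannot influence the delay.** This is too absolute. The type of person may stand for access or preference that existed beforehand. The article also does not define where the interval ends; the questionnaire is in S1 File, which is not shown here. If it ends at a doctor visit, seeing a healer or pharmacist first lies inside the interval and could lengthen it.
- **The time from seeking help to diagnosis has been left without a model.** Table 3 lists ten outcomes and gives example rows for four. A missing row among examples is not an error.
- **Large spurious effects are to be expected.** The z of 4.6 rests on assumed correlations of 0.3 and on 2,160 independent women. Women may skip questions, and 2,160 is reached only if every country meets its minimum. At correlations of 0.1 the effect is negligible.

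The table was read from a PDF, so a merged row cannot be fully excluded, but the text shows one row with one outcome label.

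**Conclusion.** The point holds for the number of visits before diagnosis. On the article's own division of intervals, it arises after the time to seek help has ended and should not be a predictor of it. Whether this biases the education, income and payer coefficients, and by how much, depends on how strongly delay and those characteristics affect the visit count, which the article does not report. Over the assumed correlations the induced partial correlation runs from about -0.01 to -0.10.

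For the first person consulted the conclusion is conditional: as question 21 measures it, it is known only when help is sought, so it does not belong in the main multivariable model unless the questionnaire's interval ends at a later contact.

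A reader might infer that the study's main findings are at risk. They are not: the country summaries and between-country comparisons of the key metrics do not use this model. The matter is worth correcting because it is a stated choice in a secondary, exploratory analysis and the correction is nearly free.

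**What to change.** 1. In Table 3, delete the number of visits before diagnosis from the predictors of time to seek help. If it is wanted as a predictor, use it for the outcome "Time from seeking help to obtaining a diagnosis".
2. Leave the first person consulted out of the main multivariable model for time to seek help. Report its association with help-seeking time descriptively or in a sensitivity model. It may stay in the main model if the questionnaire's interval ends at a later contact, such as a doctor visit.
3. State in the analysis text which event ends the time to seek help.

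The cost is a table edit and a sentence. No new data are needed, and the questionnaire, recruitment and ethics approvals do not change.

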### Aim

In this study, we aim to establish a large patient experience evidence base, and characterise the key challenges and opportunities to improve survival and quality of life for women in LMICs. We will test our hypothesis that key factors vary by country, requiring bespoke potential health strategies. With the evidence obtained from this study we expect to raise the profile of ovarian cancer in LMICs. We hope to enable national teams to engage governments and health policy makers; secure extra funding for diagnostics, research and awareness campaigns; and improve support for women. Examples of this type of approach have been successfully undertaken in high-income countries [25–28].

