### Sample size

The minimum sample size for each country is based on GLOBOCAN estimates of five-year disease prevalence in the country, producing results at the 95% confidence level (+/- 10%) [2]. CLCs can choose to recruit more patients to improve confidence intervals in their standalone results. In total, the study aims to collect data from at least 1534 women, which would provide results at a 95% confidence level, +/- 2.5%, based on global five-year prevalence. Should each of the 24 countries (3 low, 11 lower-middle and 10 upper-middle income countries) collect their minimum data, the sample size would be 2,160 (Table 2).

**Table 2 pone.0298154.t002:** Expected sample sizes by country and income level.

REGIONAL AREA	COUNTRY	WORLD BANK INCOME STATUS (JUNE 2021) [29]	MINIMUM SAMPLE SIZE	PREFERRED SAMPLE SIZE	FIVE-YEAR PREVALENCE OF OVARIAN CANCER
**Sub-Saharan Africa**	Ghana	Lower-middle	92	327	2190
	Kenya	Lower-middle	92	330	2314
	Malawi	Low	79	203	431
	Mozambique	Low	70	155	259
	Nigeria	Lower-middle	95	361	6079
	South Africa	Lower-middle	94	347	3559
	Uganda	Low	89	297	1242
	Zambia	Lower-middle	78	197	403
**North Africa**	Egypt	Lower-middle	95	364	6854
	Morocco	Lower-middle	93	340	395
**South-East Asia**	Malaysia	Upper-middle	94	357	4989
	Vietnam	Lower-middle	95	346	3468
**Western Asia**	Kazakhstan	Lower-middle	93	343	3207
	Uzbekistan	Lower-middle	92	322	1997
**Caribbean, Central, South America**	Argentina	Upper-middle	95	362	6192
	Brazil	Upper-middle	96	377	18912
	Colombia	Upper-middle	95	362	6344
	Guatemala	Upper-middle	83	236	604
	Jamaica	Upper-middle	72	165	290
	Mexico	Upper-middle	95	374	13529
	Peru	Upper-middle	93	345	3398
**South-central Asia**	Bangladesh	Lower-middle	95	364	7044
	India	Lower-middle	96	383	103716
	Nepal	Lower-middle	89	297	1297
Total		Lower-middle	2160	6815	198,713

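### Income-group comparisons are to be tested on individual women as if independent, although income group is a property of 24 countries, only 3 of them low-income

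*Protocol article*

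**What the plan says.** All references are to the protocol article.

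- **Groupings.** The Data analysis section examines key metrics "by country, region and by the socio-economic country group". It adds: "In addition, we will explore associations between patient and country characteristics and key outcome measures".
- **Inference.** The text after Table 3 states: "We will perform descriptive and inferential statistics, overall and by country and economic grouping using statistical softwares such as STATA and R". Economic grouping is therefore explicitly a basis for inference. Region is not in that sentence.
- **Tests.** For categorical variables, chi-squared or Fisher's exact tests are "used to compare proportions between groups". For the rest: "Tests, such as Kruskal-Wallis, will be applied to continuous variables".
- **Regression.** The text promises appropriate approaches and adds: "Binary, ordinal or nominal regression will be used depending on the nature of the outcome variable". It says nothing on how country or site enters the models.
- **Hypothesis.** The Aim section states: "We will test our hypothesis that key factors vary by country, requiring bespoke potential health strategies".
- **Size.** The Sample size section states: "Should each of the 24 countries (3 low, 11 lower-middle and 10 upper-middle income countries) collect their minimum data, the sample size would be 2,160".

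The Sample selection and Discussion sections provide for stratified or sensitivity analyses by selection method. Those deal with selection bias. They do not deal with the grouping of women within countries.

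**The concern.** Every woman in a country carries the same income label. Whatever else sets her country apart (health system, referral pattern, the sampling model chosen by the country lead) is carried into the income group along with the label. A chi-squared or Kruskal-Wallis test on women measures the gap between groups against sampling variation among women only. It makes no allowance for which countries happen to make up each group. The plan itself expects country differences, so independence within an income group fails on its own premise.

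More recruitment does not cure this. Larger country samples shrink the within-country part of the error, which the test counts, and leave the between-country part, which it ignores. The number of countries stays at 24.

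At stake is a statement that an outcome differs by income level. The Aim section wants the evidence used with governments and policy makers, and a false statement of that kind could point them in the wrong direction.

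**Working it through.** **The plan's own figures.** The global target follows from the simple-random-sample formula with finite population correction, n = n0 / (1 + (n0 − 1)/N), where n0 = 1.96² × 0.25 / e².
- With e = 0.025, n0 = 1,536.6. With N = 823,000 (Introduction), n = 1,533.7, which rounds up to the stated 1,534.
- The Table 2 minimums add up to the stated 2,160.

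Both reproduce, and neither contains a design effect.

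**Inputs.**
- Women per country: Table 2 minimums, 70 to 96, mean 2,160/24 = 90.
- Income groups by the Table 2 rows: low, 3 countries and 238 women; lower-middle, 13 and 1,199; upper-middle, 8 and 723. The text gives 3/11/10 instead. The two splits give nearly the same error rates.
- Assumed: true proportion 50%, and a between-country SD of 0 to 15 points. The documents give no SD. At a proportion of 50%, an SD of 5 points is an intraclass correlation of 0.05²/0.25 = 0.01.
- Assumed: two-sided 5% level, in line with the 95% confidence level in the Sample size section.

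**Check by hand, low versus upper-middle income.**
- Variance if women are independent: 0.25/238 + 0.25/723 = 0.001396. Half-width: 1.96 × √0.001396 = 7.3 points.
- Variance with country variation: 0.001396 + SD² × (1/3 + 1/8).
- SD 5 points: 0.001396 + 0.001146 = 0.002542, half-width 9.9 points.
- SD 10 points: 0.001396 + 0.004583 = 0.005979, half-width 15.2 points.

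These use the normal quantile 1.96. Small-sample degrees of freedom would widen the last two further.

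**Simulation across the three income groups.** Country proportions were drawn as 0.5 + SD × N(0,1), with binomial counts at the Table 2 sizes and no true income effect (20,000 replicates). The country-level comparator is a one-way ANOVA on the 24 country proportions.

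| Assumed SD (points) | Chi-squared, minimum sizes | Chi-squared, preferred sizes | Country-level ANOVA, minimum sizes |
|---|---|---|---|
| 0 | 5% | 5% | 6% |
| 3 | 10–11% | 24% | 5% |
| 5 | 20% | 45–46% | 5% |
| 10 | 50–51% | 79% | 5% |
| 15 | 71% | 89% | 5% |

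Drawing country proportions from a beta distribution instead gave the same picture: 12% at an intraclass correlation of 0.005, 20% at 0.01 and 57% at 0.05. Results at a true proportion of 20% were nearly identical.

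**Region, only if tested.** Across the six regions of Table 2 at the minimum sizes, the chi-squared test rejects in about 32–34%, 79–80% and 95% of studies for SD 5, 10 and 15 points.

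**The case against.** The strongest reply is that the 24 countries are a fixed set. They came from a target list and professional networks, and each has its own sample size, so they act as strata. On that view women are the sampling units, a comparison of income groups only describes these countries, and country differences do not inflate the error. This stands for purely descriptive use. It does not cover a reading in terms of income level, and the Data analysis section invites that reading when it sets out to relate outcomes to country characteristics.

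Several stronger claims are tempting, and the document does not support them:

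- **That the regression is wrong.** A reader might infer ordinary regression. The text says only that approaches will be appropriate and chosen by outcome type, and a mixed logistic or ordinal model fits that wording. The detail may stand in an analysis plan that is not shown.
- **That regional tests are certainly invalid.** Region is among the groupings to be examined but is missing from the inferential sentence. Testing it is a possible reading, not a stated plan.
- **That the main hypothesis fails.** The stated hypothesis concerns variation between countries. Country clustering does not inflate a country-versus-country test; only clustering within sites could.
- **That these are the study's headline results.** The document does not rank them so.
- **That the error is large whatever the data.** Its size rests on an SD that nobody has given. At 3 points the rate roughly doubles; at 10 points it is tenfold.

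It is also fair to say that this is a cross-sectional survey with convenience sampling, and that the Discussion already concedes selection bias and wide country-level intervals. That lowers the weight any one p-value should carry. It does not make the named tests suitable for this comparison.

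**Conclusion.** The concern holds for comparisons by economic grouping. The document commits to inference there and names tests that use the wrong unit. This is a stated analysis that does not fit the stated comparison, not a detail left for later.

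The direction is certain whenever countries differ and the result is read as associated with income level. Under the stated assumptions the real error rate is two to ten times the nominal 5% for SDs of 3 to 10 points, and higher at the preferred sizes. The same fault would affect region if it is tested, and any country-level predictor analysed without allowing for country. It does not extend to the test between countries, and it does not show the regression plan to be wrong.

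**What to change.** Change the analysis wording in four places.

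1. For income-group comparisons, for region if it is tested, and for any country-level predictor, base inference on the country as the unit. Two routes serve:
   - analyse the 24 country estimates, with 24 − 3 = 21 error degrees of freedom for income group and 24 − 6 = 18 for region;
   - fit a mixed model with a random intercept for country and small-sample degrees of freedom. Add site where countries have several sites; in a single-site country the two levels cannot be separated.
2. Label chi-squared, Fisher and Kruskal-Wallis results across these groups as descriptive of the 24 participating countries.
3. State in the regression text that models account for country.
4. State whether region will be tested or only described.

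No new data are needed and the models are only slightly more complex. The price is wider intervals and fewer significant group differences. Contrasts with the low-income group will rest on 3 countries, and the reports should say so.
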